**Figure 1 F1:**
[figure not shown]
Flowchart of trial design summary.

### Patient and public involvement

Senior citizens were involved in several stages of this project, including the relevance of the study, developing the research question, the study design and conduct of the trial. The older representatives (Denktank 60+) partnered with us on the information material, the questionnaires and the burden of the questionnaires from a patient perspective. Once the trial has been published, participants will be informed of the results in a study newsletter suitable for the public.

### Eligibility criteria

Eligible participants must have the following characteristics:60 years or older.Admitted to the hospital for a medical or surgical reason.Experiencing or complaining about new onset or aggravated sleep problems during hospital admission, for which a pharmacological intervention is needed based on the judgement of the attending physician.Ability to fill out a sleep questionnaire.

People with the following characteristics are not eligible:Inability to speak, understand or write Dutch.Lack of decision-making capacity.Previously diagnosed dementia.Transferred from another hospital to one of the study centres, with insufficient information on previous use of sleep medication.Expected stay in hospital of <48 hours.Concurrent use of sedative for a sleeping disorder (>2 dosages in the last week), such as benzodiazepine, non-benzodiazepine (Z-drugs) or melatonin.Alcohol consumption >13 units/week for women and >20 units/week for men.Drug interactions with melatonin or contraindications for benzodiazepine use.

First selection of eligible patients will be done by the attending physician, if eligible the physician will inform the research team. Final selection will be done by a member of the research team, who also will recruit eligible participants and include them after written informed consent for participation has been obtained.

### Randomisation and blinding

After patients have given informed consent, participants will be allocated randomly to either temazepam, melatonin or placebo capsules (ratio is 1:1:1). Randomisation is stratified per centre and department, the strata include the four centres (AMC, Gelre hospitals Apeldoorn, MCL and UMCG) and departments (surgical vs medical). A stratified block randomisation made by an independent statistician is used and generated by the programme CASTOR Electronic Data Capture (Castor EDC, Ciwit BV, Amsterdam, the Netherlands, 2017). The researchers are not informed about the block sizes.

All medication used in the study will appear identical to ensure true blinding of the patient, attending physician, nurse and investigators. The study medication is manufactured by Tiofarma, Oud-Beijerland, the Netherlands and will be distributed to the study sites’ pharmacies. Study medication must be kept intact at all times; the capsules cannot be broken. All study medication is packed in Single Unit Supply packages, blinded and dispensed by site trial pharmacists. The dispensing pharmacist will record the patient, patient ID and assigned medication by the randomisation process. Storage, delivery, dispensing and destruction of medication will adhere to Good Clinical Practice regulations (ICH-GCP).^34^

At the end of the study, when all data are collected, the data manager will lock the database. The information of the study arm (melatonin, temazepam and placebo) will be masked by the data manager, after which analysis can be performed in a blinded way by the researchers. Randomisation method will be broken when the study team has declared the data analysis finished.

In case of emergencies or urgent situations, such as anaphylactic reactions or loss of consciousness, and knowledge of the actual treatment is essential for further patient management, the blinding of the treatment of an individual participant can be broken (unblinded). In this case, the attending physician will contact the trial pharmacist to disclose the blinding of the study treatment for this individual patient.

### Intervention

After randomisation, all participants receive the allocated medication once daily which is in the evening before sleep (ante noctem). Study medication will be administered orally starting on the day of study enrolment.

Melatonin 1 mg and temazepam 10 mg will be used as study medication. The dosage of 1 mg melatonin is chosen based on a recent systematic review, to best mimic the normal physiological circadian rhythm of melatonin by avoiding prolonged supra-physiological blood levels in case of higher dosages.^35^ The dosage of 10 mg temazepam is the recommend dose for older patients.^36^

Study medication will be continued to either a maximum of 10 days, or 12 hours before hospital discharge, or after three consecutive nights of good sleep, or until participant decides to withdraw from the study. In case sleep problems do not resolve with study medication, the dosage can be doubled. This decision will be left to the patient’s attending physician. Attending physicians are instructed only to consider a double dose when the patient has slept badly for two nights in a row, in case there are no environmental or treatable physical factors that could cause the poor quality of sleep (QOS) and they should take possible adverse effects of study medication into account. Double doses of study medication will be registered in the case report form and in the medical record.

Study medication will be discontinued if a condition occurs that needs treatment with benzodiazepines (eg, anxiety), if events occur that imply a higher risk of adverse events (eg, respiratory insufficiency or starting chinolones) and in case of persisting sleeping problems. Persisting sleep problems is defined as self-reported poor QOS for three consecutive nights after study medication has been doubled.

After study medication is discontinued, either due to a reason listed above or due to end of study period, treatment will be provided according to the hospital’s protocol and under the responsibility of the attending physician. Patients remain in the study and follow the study protocol, except for using study medication.

### Timing of measurement and outcome measures

Demographic data, such as age, sex, nationality, highest educational status and living situation will be collected at baseline. Medication use, blood tests 24 hours prior to study inclusion or 24 hours after study inclusion, severity of foregoing sleep problems, depression and anxiety, level of independence, health status and vulnerability (eg, fall risk) are measured at baseline. Primary and secondary outcome measures will be recorded at baseline (T0) and every day until the 10th day (T1–T10) or until discharge. Table 1 provides an overview of the timing of measurements and the outcome measures.

**Table 1 T1:** Overview of the timing of measurements and outcome measures

Measurement	Description and instrument	Timepoints		
		Baseline	Daily	Discharge
Sleep quality	*Leeds Sleep Evaluation Questionnaire (LSEQ)*,^38 44^ 10-item questionnaire, self-rated, on 0–100 mm line. Validated tool for measuring changes in sleep on four domains; getting to sleep, quality of sleep, ease and awakening from sleep and alertness and behaviour following wakefulness The Dutch version of the LSEQ is forwards and backwards translated according to the translation guidelines^45^	x	x	
	Numeric rating scale for overall sleep, an overall numeric rating of quality of sleep. With ‘0’ representing a very bad night’s sleep and ‘10’ representing a very good night’s sleep	x	x	
Sleep pattern	*The core consensus sleep diary* 46, a 10-item sleep log to gain insight in the sleep pattern of a participant	x	x	
Factor influencing sleep	Based on literature,^15 47–50^ an overview is made of 10 influencing factors on sleep in hospitals. Participants can indicate whether these factors influenced their sleep and if so, to what extent	x	x	
Objective sleep parameters	*Actigraphy, MotionWatch 8,* a wristwatch-like device, worn on the non-dominant hand. The actiwatch registers motion in epochs of 30 s. Based on motion sleep latency, sleep efficiency, number and duration of wake bouts, time awake after sleep onset in minutes can be calculated	x	x	
Cognition	*Mini-Mental State Examination* 51, a 10-item screening tool to evaluate global cognitive function	x	x*	
	*Stroop Colour-Word test* 52 53, *consists of three subtasks. Used to measure attention, processing speed, cognitive flexibility and working memory*	x	x*	
	*The Trail Making Test (TMT) A&B* 54 55, *consists of two subtasks, is used to measure visual search, attention, divided attention, processing speed and cognitive flexibility*	x	x	
Assessment of delirium	*4 AT,* 56 a four-item screening tool to detect attention deficits due to delirium	x	x†	
	*DSM-V,* 57 *the Diagnostic and Statistical Manual of the American Psychiatric Association (DSM-5) the most widely used nomenclature by clinicians and researchers for the classification of delirium*	x‡	x‡	
Severity of sleep problems	*Insomnia severity index*,^58^ a seven-item questionnaire, self-rated, to quantify perceived insomnia severity	x		
Depression and anxiety	*Hospital Anxiety Depression scale* 59, a 14-item questionnaire, self-rated, consisting of two seven-item subscales looking at depression and anxiety	x		
Level of independence	*Katz-15 Activities of Daily Living (ADL) index scale,* 60 61 the modified Katz ADL index 15-item scale, answered with ‘yes’ or’ no’ to evaluate the level of independence	x		
Health status	*Rotterdam symptom check list (RSCL)* 62, a 30-item questionnaire, self-rated, to assess physical and psychological symptom	x	x§	
	*Charlson comorbidity index (CCI),* 63 a classification method for comorbid conditions. It is a valid method to estimate risk of death comorbid disease in 1 year			x
Vulnerability (eg, fall risk)	Safety management system patient screening^64^	x		
Adverse events	Confusion, delirium, reduced consciousness, falls, aspiration, other additional adverse events (in complication register) and length of hospital stay in days		x	

*On day 3 Stroop Colour-Word test and TMT are repeated with daily assessment.

†Administered if a delirium is suspected.

‡When score on 4AT deviates, detailed assessment of mental status with DSM-V to reach diagnosis of delirium.

§On day 4 RSCL is repeated with daily assessment.

#### Primary outcome

The primary outcome of the study is change in self-reported sleep quality during the treatment period (T0–T10). Sleep quality will be assessed with the Leeds Sleep Evaluation Questionnaire (LSEQ).^37 38^

#### Secondary outcomes

Change in self-reported sleep measures: getting to sleep, awakening from sleep and behaviour following wakefulness during treatment period will be assessed with the other subscales of the LSEQ. These measures will be assessed on T0 until T10.Objective sleep parameters. To assess objective sleep parameters participants will wear a MotionWatch eight during the study period (T0–T10). This wristwatch-like device will calculate sleep latency, sleep efficiency, number and duration of wake bouts, time awake after sleep onset in minutes based on motion of the patient.Number of good night sleep. Good nights of sleep will be assessed with a numeric rating scale for QOS. On the numeric rating scale ≤4 is considered a bad night’s sleep, 5–6 is neither a good or bad night’s sleep and ≥7 is a good night’s sleep.^39^
Time needed to reach improvement in self-reported sleep quality will be based on the LSEQ as well. Improvement of sleep quality is defined as the first day that an improvement of 10 mm is reached compared with baseline.Adverse events defined as confusion, delirium, reduced consciousness, falls, aspiration and other additional adverse events will be monitored daily on T0–T10.Length of hospital stay in days will be recorded at discharge.

To ensure consistency and optimisation of the data collection process, all members of the research team who will include patients in the study will follow a training how to conduct measurements according to Standard Operating Procedures and how to fill out the Case Report Forms. Non-adherence to the study protocol will be obviated as much as possible. However, when it occurs this will be registered by the research team.

### Sample size calculation

Sample size calculation is based on the primary outcome measure QOS, assessed with the LSEQ. To establish a clinically relevant observed effect of melatonin, temazepam or placebo a difference of 10 mm on the QOS was chosen.^40^ The SD was calculated based on the SE presented in this study. To detect a mean difference of 10 mm, two-sided, with a power of 80% and significance level of α<0,05, we need at least 210 patients per group (total of 630 patients).

The expected dropout rate during study period is 5%.^41^ Therefore, we should recruit at least 663 patients, with 221 patients in each study arm.

### Data analysis

Data will be analysed according to an intention-to-treat principle. Researchers are not aware of the allocation of the intervention and therefore analyses will be conducted in a blinded way. A per-protocol analysis will be conducted excluding patients that did not receive the intervention according to protocol and were incorrectly included in the study. To determine the effects of temazepam, melatonin or placebo on sleep quality, linear mixed models will be used. Analysis will be performed on change of sleep quality over time taking baseline value into account (ie, night before start of study medication). The following covariates will be added to the model: age, gender, different concurrent medication (eg, morphine), severity of disease diagnosis (Rotterdam Symptom Checklist (RSCL), pain severity (visual analogue scale, RSCL), acute or elective admission to the hospital, foregoing sleep problems (insomnia severity index), number of patients in the room, level of independency (Katz Index of Independence in Activities of Daily Living), level of anxiety (Hospital Anxiety Depression scale) and days in the hospital before inclusion. Linear mixed models will also be used to evaluate getting to sleep, awakening from sleep, behaviour following wakefulness and the objective sleep parameters measured with actigraphy. Analyses of the time needed to reach improvement of sleep quality will be done with an interval-censored survival analysis. Proportion of good nights of sleep measured with the numeric ratings scale will be analysed, when normally distributed, with multiple linear regression analysis. For the analysis of adverse events related to study medication, descriptive statistics will be used to show which adverse events occurred. Depending on the occurrence of these adverse-events and distribution, log-linear analysis, Poisson or multiple regression analysis will be used. Time to occurrence of an adverse event will be analysed with Cox regression.

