## Discussion

Although sleeping problems are a common complaint in hospitalised older patients, there is still no evidence based pharmacological treatment available. Most studies on (non-)pharmacological treatment of sleeping problems in older patients were performed in community dwelling older people. However, sleep quality in hospitalised elderly is influenced by other factors than community dwelling older people and might require other therapeutic regimes.^42^ For example, light and noise in the room influences the QOS in hospitalised older patients and it is difficult to measure, subsequently standardise for these confounders on the ward. In order to minimise the effect of these potential confounders, we stratified randomisation, in which patients are randomised by hospitals and departments. In this way, the known and unknown confounders are randomised and equally distributed among the groups.

In this study it was not possible to measure sleep quality and quantity using polysomnography, which is the gold standard to measure sleep quality and quantity. Instead of polysomnography, we measured objective sleep parameters indirectly by using an actigraphy, in addition to the self-reported sleep outcome measures.

This study is the first large randomised controlled trial on the effects of melatonin, temazepam or placebo in hospitalised older patients, which aimed to establish an evidence based pharmacological treatment for sleeping problems in older hospitalised patients. Irrespective of the results of this trial, the outcomes can be used for developing clinical guidelines for the treatment of sleep problems among hospitalised older patients.

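### The primary mixed model lists eleven covariates but neither randomisation stratum (centre, surgical/medical department), so reported standard errors may be slightly too large and the test slightly conservative

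*Protocol article*

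**What the plan says.** Under Randomisation and blinding, the protocol article states: "Randomisation is stratified per centre and department, the strata include the four centres", with department split into surgical and medical. That gives 4 × 2 = 8 strata. The method is blocked within strata: "A stratified block randomisation made by an independent statistician is used".

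The Discussion gives the reason. Light and noise on the ward affect sleep and are hard to measure or standardise, and so: "In order to minimise the effect of these potential confounders, we stratified randomisation, in which patients are randomised by hospitals and departments".

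Under Data analysis, the primary method is stated as: "To determine the effects of temazepam, melatonin or placebo on sleep quality, linear mixed models will be used", with the baseline value taken into account. The adjustment set follows as an explicit list. It opens with "The following covariates will be added to the model: age, gender, different concurrent medication (eg, morphine" and closes with "level of anxiety (Hospital Anxiety Depression scale) and days in the hospital before inclusion". In between come disease severity, pain, acute or elective admission, earlier sleep problems, room occupancy and independence. That makes eleven items, without centre or department. No fixed or random effect for either factor appears elsewhere in the article.

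**The concern.** Blocking within strata balances the arms inside each centre-by-department cell. Differences between cells then cancel out of the treatment comparison, and its true sampling variance no longer contains the between-stratum component. A model without the strata still counts that component as residual error, so it reports a standard error larger than the true one. Confidence intervals become wider than they need be, and the test rejects less often than its nominal level.

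The article's own reasoning makes the omission notable. The sponsor stratified because hospital and ward conditions were expected to influence the outcome and could not readily be measured. Centre and department are the available proxies for those conditions, and they are the two variables that the detailed list leaves out.

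**Working it through.** **Inputs from the protocol article.** 10 mm difference, two-sided 5% level, 80% power, 210 patients per group (Sample size calculation); 1:1:1 allocation in stratified blocks over 8 strata (Randomisation and blinding).

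**Not in the article.** The SD, the block size, and r. Here r is the share of the residual variance of the patient-level outcome, after baseline and the listed covariates, that the strata explain. It is assumed at 1%, 5% and 10%.

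**Step 1: the plan's own figure.** The 210 per group cannot be reproduced independently because the SD is not stated. Solving for it gives SD = 10 × √(210/2) / (1.960 + 0.842) = 36.6 mm. This value is used below as the residual SD. It affects only the power figures, not the standard-error ratio or the type I error.

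**Step 2: standard errors.**
- Reported without strata: 36.6 × √(2/210) = 3.57 mm.
- True under stratified blocks: 3.57 × √(1−r).
- Ratio: 1/√(1−r).

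**Step 3: type I error and power.**
- Type I error without strata: 2 × [1 − Φ(1.96/√(1−r))].
- Power without strata: Φ[(10 − 1.96 × 3.57) / (3.57 × √(1−r))].
- Power with strata: Φ[10 / (3.57 × √(1−r)) − 1.96].

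| r (assumed) | Reported SE too large by | Type I error, strata omitted | Power, omitted | Power, included | Points forgone |
|---|---|---|---|---|---|
| 0% | 0% | 5.0% | 80.0% | 80.0% | 0 |
| 1% | 0.5% | 4.9% | 80.1% | 80.4% | 0.3 |
| 5% | 2.6% | 4.4% | 80.6% | 82.0% | 1.4 |
| 10% | 5.4% | 3.9% | 81.3% | 84.0% | 2.7 |

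**Step 4: simulation check.** Settings: 630 patients, 3 arms, 8 strata of equal expected size, assumed blocks of 6, one endpoint per patient, no other covariates, 4000 runs per setting. At r = 10%:
- Strata omitted: mean reported SE 3.57 against an empirical SD of the estimate of 3.40; type I error 3.5%; power 80.9%.
- Strata included: 3.38 against 3.40; type I error 4.6%; power 84.4%.

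The empirical SD is 3.40 under both models, so the estimate itself is equally precise and only the reported uncertainty differs. At r = 2% the simulated type I errors (5.15% omitted, 5.5% included) are within or close to simulation noise, whose standard error is √(0.05 × 0.95/4000) = 0.34 points. An effect that small cannot be seen in 4000 runs.

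**Step 5: what r refers to.** The formula needs the share of the total variance of the patient-level summary, which includes within-patient noise. A share of between-patient variance alone must be scaled down. As an illustration, assume an intraclass correlation of 0.5. The between-patient part of a five-night mean is then 0.5/(0.5 + 0.5/5) = 0.83, so 5% to 10% of between-patient variance becomes r = 4.2% to 8.3%. With a single night the part is 0.5, and r = 2.5% to 5%.

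**The case against.** The strongest reply is that r may be close to zero. The model takes baseline into account, and baseline is the night before study medication in patients whose sleep problem arose or worsened in hospital. A stable hospital or ward effect is present in that night too and would be largely absorbed. Room occupancy, acute or elective admission, concurrent medication, pain and disease severity may also track ward and specialty. This stands as an argument about size. It is why the range starts at 1%, where the effect is negligible. It does not make those covariates a substitute for the two factors the trial randomised by.

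A second reply is that the article is condensed and silent on random effects, so an unseen plan might place centre there. That is possible. But the article does not defer the adjustment set. It sets out a detailed list, and both design factors are missing from it.

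A reader might also infer more than the article supports:
- *That the treatment estimate is biased or false positives rise.* Neither follows. Allocation is balanced within strata, and the error is on the conservative side.
- *That the precision bought by stratifying is lost, as if patients had been discarded.* The estimate has the same sampling variability under both models. What is affected is the reported interval and the test.
- *That the trial becomes underpowered.* With the SD implied by 210 per group, power without the strata stays at or above 80% throughout the range.
- *That every secondary analysis has the same omission.* The article says mixed models will be used for the other LSEQ subscales and actigraphy but does not state their covariates.

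**Conclusion.** The point holds in a limited form. The published covariate list for the primary mixed model omits both stratification factors. If they explain any residual variance, the reported standard error is too large and the test is conservative. This is a modest inefficiency in reporting and does not threaten validity.

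The direction follows from the design. The size cannot be fixed from the article and rests on the assumed r: it is negligible near 1% and reaches a 5.4% overstatement of the standard error at 10%. The power figures also assume a residual SD of 36.6 mm, and all the figures treat the outcome as one summary per patient. The correction is worth making because it costs almost nothing.

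**What to change.** Add one sentence to the Data analysis section, for example: *Centre (four levels) and department (surgical or medical) will be included as fixed effects in the linear mixed model for LSEQ quality of sleep, and in those for the other LSEQ subscales and the actigraphy measures.* The eight-level stratum may be used instead. The choice between the two forms should be settled before the database is locked.

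The cost is 3 + 1 = 4 degrees of freedom for the two main effects, or 7 for the eight-level stratum, with 630 patients planned for analysis. Both factors are known at randomisation, so no new data are needed and the sample size does not change.

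### The good-nights regression does not state that it adjusts for the T0 numeric rating, which is scheduled for every patient; adding it is a minor, free gain in precision

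*Protocol article*

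**What the plan says.** Under Secondary outcomes, "Good nights of sleep will be assessed with a numeric rating scale for QOS", with 7 or more counted as good. Table 1 lists this instrument ("Numeric rating scale for overall sleep, an overall numeric rating of quality of sleep") with a mark under both baseline and daily, and the text above the table says: "Primary and secondary outcome measures will be recorded at baseline (T0) and every day until the 10th day (T1–T10) or until discharge". A pre-treatment value on the outcome's own scale is therefore scheduled for every patient.

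The Data analysis section treats two sleep outcomes differently:

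- **Sleep quality (LSEQ), mixed model.** "Analysis will be performed on change of sleep quality over time taking baseline value into account (ie, night before start of study medication"). Then "The following covariates will be added to the model", followed by eleven items. The item closest to baseline sleep is "foregoing sleep problems (insomnia severity index), number of patients in the room", where the insomnia severity index is a different instrument.
- **Good nights.** "Proportion of good nights of sleep measured with the numeric ratings scale will be analysed, when normally distributed, with multiple linear regression analysis". No baseline value and no covariate is named.

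**The concern.** A patient's rating before treatment is likely to predict how many later nights reach 7 or more. If the model leaves it out, stable differences between better and worse sleepers stay in the residual. The interval for the arm comparison is then wider than the collected data allow, and a chance imbalance in T0 sleep is not corrected.

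Carrying the printed covariate list over to this model would not settle the matter, because the T0 numeric rating is not on it.

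It is also open whether the T0 night counts in the proportion. The Objectives section defines the outcome over the study period, and Secondary outcomes labels the study period T0–T10 when describing actigraphy. Counting a pre-treatment night would dilute any treatment effect.

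**Working it through.** **No figure to reproduce.** The protocol gives no power, effect size, SD or correlation for good nights. Its 210 per group and 80% power belong to the LSEQ primary outcome. They are borrowed below only as a frame, and every other input is an assumption.

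**Step 1: formula.** Adjusting for a baseline value that has (partial) correlation ρ with the outcome multiplies the residual variance by 1 − ρ². If power without it is 80% (two-sided 0.05), power with it is

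Φ((1.960 + 0.842)/√(1 − ρ²) − 1.960).

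For ρ = 0.3: 2.802/√0.91 = 2.937; 2.937 − 1.960 = 0.977; Φ = 83.6%, a gain of 3.6 points. In the same way, the gain is 0.4 at ρ = 0.1, 1.6 at 0.2, 6.4 at 0.4, 9.9 at 0.5 and 13.8 at 0.6.

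**Step 2: plausible ρ.** Eligibility requires patients to be "Experiencing or complaining about new onset or aggravated sleep problems during hospital admission", to a degree judged to need drug treatment. That narrows the T0 range and lowers ρ. Nightly 0–10 ratings were simulated with SD 2.2, mean 4 at T0 and 6 afterwards, 2–10 follow-up nights, and a good night at 7 or more. Each cell gives ρ between T0 and the later proportion, then the gain from 80%:

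| Within-patient correlation | T0 unrestricted | T0 ≤ 6 | T0 ≤ 4 |
|---|---|---|---|
| 0.2 | 0.28, +3.1 | 0.23, +2.1 | 0.18, +1.2 |
| 0.3 | 0.39, +6.0 | 0.32, +4.0 | 0.24, +2.4 |
| 0.4 | 0.49, +9.3 | 0.40, +6.3 | 0.31, +3.7 |
| 0.5 | 0.57, +12.7 | 0.48, +9.1 | 0.36, +5.3 |
| 0.6 | 0.65, +15.7 | 0.55, +12.0 | 0.41, +6.8 |

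**Step 3: direct power simulation.** Inputs: 210 per arm, rating SD 2.5, mean 5, a 0.5-point effect, 2–10 nights, least squares with and without T0, 1,500 replicates. Results are for within-patient correlation 0.3, then 0.5:

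- T0 unrestricted: 71% to 80%; 64% to 80%.
- T0 ≤ 6: 77% to 81%; 71% to 77%.
- T0 ≤ 4: 76% to 77%; 68% to 71%.
- T0 ≤ 6, with an insomnia-index-like covariate already in the model (assumed correlation 0.5 with the patient effect): 79% to 81%; 73% to 77%.

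A fresh run with 2,000 replicates gave restricted gains of 2 and 8 points (T0 ≤ 6) and 2 and 4 points (T0 ≤ 4), so individual gains carry a few points of simulation error.

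**Step 4: counting the T0 night.** If k treated nights are averaged together with one untreated night, the difference in proportions for those patients shrinks by k/(k + 1): 2/3 = 0.67 at two nights, 10/11 = 0.91 at ten.

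**The case against.** The strongest reply is that silence is not a decision. A reader might infer that the analysis leaves out the T0 rating by design. The text does not support that. It excludes nothing, a multiple regression naturally suggests covariates, and the article gives only a method name for most of its other secondary analyses too. A condensed article commonly leaves such lists to the full protocol or SAP. All of this stands, and the point is accordingly that the article does not state the adjustment. What remains is specific: the one list that is printed lacks the same-scale baseline, so borrowing that list would still omit it.

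A reader might also take about 15 points as the power being lost. That figure needs unrestricted T0 and high within-patient correlation, whereas the trial enrols patients because they sleep badly. If the insomnia severity index and the other listed covariates enter the model, only the partial correlation of T0 counts, and the gain is smaller again.

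Finally, the outcome is secondary, and randomisation keeps the unadjusted comparison unbiased. That also stands, and it limits the point to efficiency.

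**Conclusion.** The point holds as a minor, free improvement and not as an error. The article does not state that the good-nights model uses the T0 rating, and its only covariate list omits it. Under assumed inputs with T0 restricted to poor sleepers, the gain is roughly 0–7 points of power, corresponding to ρ of about 0.1 to 0.4 from 80%. A mild restriction (T0 ≤ 6) with within-patient correlation of 0.5 to 0.6 can give about 8–12. About 15 requires unrestricted T0 and high correlation. The direction is secure, because a prognostic baseline value costs one degree of freedom among some 420 patients per contrast. The size is not, because the protocol supplies no correlation, SD or effect for this outcome. The documents do not support reading this as bias or as a weakness of the primary analysis, which already takes its baseline into account.

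**What to change.** Add to the Data analysis section that the good-nights model, whatever its final form, includes the T0 numeric rating as a continuous covariate, and that the T0 (pre-treatment) night is used only as that covariate and is not counted in the proportion. If the full protocol or SAP already says this, confirming it is enough.

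The cost is one clause and one degree of freedom, with no new data. Stating it before unblinding also avoids choosing covariates after the results are known.
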